##### Recovery trajectories

Generalised linear mixed models (GLMMs) and latent class trajectory modelling will be used to examine stability and change in recovery trajectories for the longitudinal PROMs data, and to identify homogeneous clusters of patients with contrasting clinical phenotypes. Time since registration with the programme will initially be included as a linear covariate, but we will explore the functional form of the effect of time to allow for phenomena such as a plateau in symptom recovery or a period of sudden rapid improvement or relapse. Models will include random slopes and intercepts, allowing for individualised differences in severity of baseline symptoms and subsequent trajectories. Fixed effects will include age, gender, ethnicity, IMD and educational attainment.

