## Background

Since the emergence of the new coronavirus, SARS-CoV-2 in Wuhan, China in December 2019^1^ and the subsequent COVID-19 variants, it has become apparent that while many affected people make a full recovery, others are left with long-term disabling and distressing symptoms,^2^ known as ‘long COVID-19 syndrome’.^3 4^ Prevalence estimates vary, but at least 50% of hospitalised^5 6^ and 10% of non-hospitalised continue to have symptoms 12 weeks after the initial infection.^2 4^ UK government figures suggest that by the end of July 2021, 5.9 million people in the UK had tested positive for COVID-19, of whom just under half a million (492 933) had been admitted to hospital (https://coronavirus.data.gov.uk/), suggesting that over 750 000 people in the UK may experience disabling symptoms persisting more than 12 weeks.

The pathophysiology of long COVID-19 has yet to be elucidated. It appears to be a multisystem disorder, characterised by variability in symptoms and a fluctuating trajectory,^4^ which significantly impairs people’s ability to work, look after their children, or engage with other activities. Despite variability in the nature and severity of reported symptoms, there are some core symptoms experienced by nearly all those with kong COVID-19: fatigue; cognitive impairment (‘brain fog’); breathlessness; anxiety and depression.^2^ These core symptoms are present in numerous other long-term conditions, and treated with well established, non-pharmacological interventions, including physiotherapy, nutritional advice, cognitive behavioural approaches, sleep hygiene and improving self-management skills. These interventions are most often delivered by Allied Health Professionals (AHP), such as physiotherapists, occupational therapists, clinical psychologists and dieticians, specialising in rehabilitation.

Prior to the COVID-19 pandemic, rehabilitation services were at capacity, and their ability to absorb over half a million additional patients requiring help has been further compromised by redeployment of many AHP to supporting acute services. Additionally, many services are system-focussed, so a patient with long COVID-19 who is breathless, fatigued and anxious could be directed to three different clinicians: a respiratory physiotherapist to help with breathing, a neurophysiotherapist or occupational therapist for fatigue, and a clinical psychologist for anxiety, making treatment extremely burdensome.^7^

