#### Data collection

Quantitative data on numbers of patients, HCPs and long COVID-19 clinics registered to use LWCR. Additionally, patient demographic data, clinical and service data and app usage patterns, as recorded through the LWCR platform will be provided.

Demographic data will be obtained on patients’ age, gender, ethnicity, highest level of educational attainment and socioeconomic status (using Index of Multiple Deprivation, calculated from the postcode) when patients first register on the app. This data will be entered by HCPs or the patients themselves.

Clinical data will be obtained from patient-completed PROMs on the app. Patients will be asked to complete all the PROMs at baseline to help with clinical assessment, and thereafter, only those PROMs which the clinician and patient deem to be clinically relevant and helpful for clinical management.

Validated PROMs include: the Work and Social Adjustment Scale which measures functional impairment and is our primary outcome measure^26^; EuroQol 5 dimensions, 5 response level instrument (EQ-5D-5L) for health related quality of life^27^; Functional Assessment of Chronic Illness Therapy - Fatigue (FACIT-F) for fatigue^28^; Generalised Anxiety Disorder Assessment (GAD-7) for anxiety^29^; Personal Health Questionnaire Depression Scale (PHQ-8) for depression^30^; Medical Research Council (MRC) dyspnoea scale^22^ and Dyspnoea-12^31^ for breathlessness, and Perceived Deficits Questionnaire-5 item (PDQ-5) for cognitive impairment.^32^ Additional questions explore levels of physical activity and overall recovery from COVID-19.

Service use data will be obtained when patients complete a service use questionnaire (every 4 weeks), detailing the number of healthcare appointments, days off work and days as a hospital inpatient they have experienced.

Usage data including the date and time of each page view by each patient are recorded automatically by the programme.

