##### Effectiveness of the LWCR programme

We will investigate the feasibility of creating a synthetic comparator arm from patients with long COVID-19 enrolled in suitable comparator cohorts, hosted in BREATHE-SAIL.^33^ Direct comparisons will be made between patients receiving the evidence-based interventions and the comparator group(s) in multivariable GLMMs with propensity score methods used to provide control for measured confounders.

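### The trajectory models name time since registration as their only clock and list neither time from infection to registration nor acute hospitalisation, so between-patient results can reflect illness stage at registration

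*Protocol article*

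**What the plan says.** All places are in the Protocol article.

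- **Clock.** Recovery trajectories: "Time since registration with the programme will initially be included as a linear covariate". The section adds that "we will explore the functional form of the effect of time to allow for phenomena such as a plateau in symptom recovery". This concerns the shape of the time effect, not its origin.
- **Covariates.** Same section: "Fixed effects will include age, gender, ethnicity, IMD and educational attainment". It also says "Models will include random slopes and intercepts, allowing for individualised differences in severity of baseline symptoms and subsequent trajectories".
- **Data.** WP3 Data collection names demographics at registration ("age, gender, ethnicity, highest level of educational attainment and socioeconomic status"), patient-completed PROMs with extra questions on activity and overall recovery, a four-weekly service use questionnaire that counts inpatient days, and page views.
- **Epidemiology.** The Background puts persistence at no less than 50% in hospitalised patients, while "10% of non-hospitalised continue to have symptoms 12 weeks after the initial infection". The Discussion says the cohort includes non-hospitalised patients.
- **Comparator.** Effectiveness of the LWCR programme proposes to look into the feasibility of a synthetic comparator arm, analysed in GLMMs with "propensity score methods used to provide control for measured confounders". The confounders are not listed and no index date is given. WP3 Participants refers to effects at 3 and 6 months.

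**The concern.** Patients can register at quite different intervals after infection. If recovery slows with time, the change expected over the next few months depends on that interval, whatever the programme does. The interval is neither the clock nor a listed covariate.

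Three planned analyses compare patients with one another and are exposed to this:

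- **Latent classes** (Recovery trajectories) are meant to show contrasting phenotypes, but may partly sort patients by illness stage.
- **Engagement dose-response** (Mediation analysis of intervention components). If early registrants engage differently and also improve faster without help, an association appears with no programme effect behind it.
- **Equality interactions** (Equality). If disadvantaged groups reach clinics later, late arrival can look like smaller benefit.

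The same gap affects any comparator analysis. Its two groups need a shared starting point, and a propensity score can balance only what was recorded.

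**Working it through.** **No stated figure bears on this point.** The check is a comparison of lists, a short piece of algebra and a labelled illustration.

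**1. Lists side by side.**

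| Variable | WP3 Data collection | Recovery trajectories model |
|---|---|---|
| Age, gender, ethnicity, IMD, education | listed | listed |
| Time since registration | registration is the start of data capture | the clock |
| Date of infection or onset | not listed | not listed |
| Admission for the acute infection | not listed; the four-weekly inpatient days are service use and are not said to cover it | not listed |

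**2. What adding the variable can and cannot do.** For patient i let D_i be the delay from infection to registration and t the time since registration. Time since infection is D_i + t. With a natural slope b and a programme slope c, both linear,

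E(Y) = a + b(D_i + t) + c·t = a + b·D_i + (b + c)·t.

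Within a patient D_i is constant, so the data on t give only the sum b + c. The two clocks are collinear. Taking b from the coefficient of D_i would require late and early registrants to differ in nothing but illness stage, which a single arm cannot show. Including D_i and D_i × t does let level and slope vary with stage, and so adjusts comparisons between patients.

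**3. Illustration A (all inputs assumed, no programme effect).** Mean score f(m) = 12 + 16·exp(−m/τ), with m in months since infection. Improvement over the next three months is f(m) − f(m + 3) = 16·exp(−m/τ)·(1 − exp(−3/τ)).

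| τ | registers at month 3 | registers at month 12 | gap |
|---|---|---|---|
| 6 | 3.82 | 0.85 | 2.97 |
| 8 | 3.44 | 1.12 | 2.32 |
| 12 | 2.76 | 1.30 | 1.46 |

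The gap is about 1.5 to 3.0 points. The bias in a comparison of two groups is this gap multiplied by the difference in their shares of early registrants. It reaches the full gap only if one group all registers at month 3 and the other all at month 12.

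**4. Illustration B (assumed).** Score = A·2^(−w/h), with w in weeks since infection and half-life h. The fall over 12 weeks from registration at week D, as a share of A, is 2^(−D/h)·(1 − 2^(−12/h)).

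| h (weeks) | D = 12 | D = 52 |
|---|---|---|
| 13 | 24.9% | 3.0% |
| 52 | 12.6% | 7.4% |

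In this curve the fall relative to the score at registration, 1 − 2^(−12/h), is the same for every D. The dependence on delay is therefore in absolute change. Curve A, which levels off above zero, does not have that property.

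**The case against.** The case on the other side is substantial.

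- **The article is condensed and its lists are open-ended.** The fixed-effects sentence does not claim to be complete, and Usage and engagement mentions baseline clinical factors. A reader might infer that the two variables are not collected at all. The documents support only that they are not listed.
- **A reader might infer that the omission is what mixes natural recovery with programme time.** It is not. The single-arm design does that. The Strengths and limitations box admits the missing comparator, and the Discussion says causal evidence must come from elsewhere. Step 2 of the working shows that the added covariate would not cure it.
- **A reader might take the 50% and 10% in the Background as a five-fold prognostic difference.** They are the shares of infected people still symptomatic at 12 weeks. They do not compare recovery among people who already have long COVID and have registered. They are a reason to record hospitalisation, not a measure of its effect here.
- **A reader might infer that the comparator can have no matching time zero.** The Effectiveness section does not say that registration is its clock, cohort members have an enrolment date, and the arm is only a feasibility question. What can be said is that no time zero is stated.
- **The illustrations assume smooth decay**, whereas the Background describes a fluctuating course.
- **Late capture is possible.** WP1 Outputs foresees app updates, including questionnaires, every few months. It would be wrong to say that the gap cannot be repaired.
- **Random slopes and intercepts are planned.** They absorb individual variation, but they do not remove confounding of the fixed effects for engagement or disadvantage.

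These points limit the finding but do not remove it. The article names a clock and a covariate set, and the profiling of heterogeneity to which it turns in place of a controlled comparison is where delay matters.

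**Conclusion.** The point holds as a weakness in a stated analysis choice. Followed as written, the between-patient results of WP3 can be confounded by illness stage at registration, and any comparator analysis lacks a stated common origin.

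The size cannot be derived from the documents. The 1.5 to 3.0 points rest wholly on curve A, on τ between 6 and 12 months and on registration at months 3 and 12. The direction, with earlier registrants showing more unaided improvement, needs only that mean recovery slows with time since infection. Actual bias also needs delay to differ by engagement or by demographic group, on which the documents give no data.

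The finding does not show that natural recovery would be separable from programme effect if the variables were added.

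**What to change.** 1. Add two registration items to the app: date of infection or symptom onset, and whether the patient was hospitalised for acute COVID-19 (yes/no). Ask patients already registered in a routine update.
2. In the GLMMs, latent-class and mediation models, include time from infection to registration with its interaction with time since registration, and hospitalisation. A flexible form such as a spline suits the first.
3. If a comparator proves feasible, define one index date for both groups, aligned on time since infection and calendar period. Start follow-up there and put both variables in the propensity score.
4. State that within-arm slopes describe recovery under the programme and are not estimates of its effect.

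The cost is two short questions and a few model terms. Onset dates will carry some recall error and some will be missing, more so when asked late or when patients have left. The planned missing-data sensitivity analyses can be extended to them.

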##### Mediation analysis of intervention components

A mediation analysis will be undertaken in which intervention components and measures of patient app usage and engagement (number of logins and assessments completed) will be added to longitudinal models as explanatory factors. We will explore whether increased engagement by clinicians, such as messages sent and reviews of patient assessments on the dashboard, is linked with improved patient outcomes. We will assess whether there is a dose–response relationship between usage of the app/introduction of new content and change in outcomes.

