**Methods and analysis:**

Mixed-methods, theoretically informed, single-arm prospective study, combining methods drawn from engineering/computer science with those from biomedicine. There are four work packages (WP), one for each objective. WP1 focuses on identifying user requirements and iteratively developing the intervention to meet them; WP2 combines qualitative data from users with learning from implementation science and normalisation process theory, to promote adoption, scale-up, spread and sustainability of the intervention; WP3 uses quantitative demographic, clinical and resource use data collected by the DHI to determine illness trajectories and how these are affected by use of the DHI; while WP4 focuses on identifying and mitigating health inequalities and overarches the other three WPs.

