#### Participants

The target for year 1 will be to recruit 1000 patients registering with the DHI. This will enable us to estimate the overall proportion of patients engaging with the app with a high-level of precision (maximum width of 95% CI is ±3.2%). Similar or increased levels of precision will be achieved when estimating the proportion of those referred who register with the intervention. The sample size in year 2 has not been prespecified and will depend on practical constraints imposed by the scale of the pandemic as the digital intervention is rolled out nationally. Power calculations will be carried out for the year 2 analyses based on the ‘pilot’ data from year 1. This will include power for the proposed quasi-experimental analysis of the effect of the DHI on outcomes at 3-month and 6-month follow-up.

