##### Usage and engagement

Patient engagement with the app will be reported using a stratification of patients into low, medium and high categories based on number of logins over the first 12 weeks. Demographic and baseline clinical factors influencing uptake and use will be identified through logistic regression, with multivariate methods used to model patterns of app engagement over time.

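### Usage is added to the outcome models without having to precede the outcome, so an app with no effect can appear helpful or harmful in the mediation and dose-response analysis

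*Protocol article*

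**What the plan says.** Under WP3, Mediation analysis of intervention components, "measures of patient app usage and engagement (number of logins and assessments completed) will be added to longitudinal models as explanatory factors". The same paragraph asks whether "increased engagement by clinicians, such as messages sent and reviews of patient assessments on the dashboard, is linked with improved patient outcomes", and looks for a dose-response "relationship between usage of the app/introduction of new content and change in outcomes". It gives no lag, landmark or ordering of usage and outcome.

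The longitudinal models are described under Recovery trajectories: "Time since registration with the programme will initially be included as a linear covariate", with random intercepts and slopes. The fixed effects named are age, gender, ethnicity, deprivation index and education. Under Usage and engagement, patients are grouped into "low, medium and high categories based on number of logins over the first 12 weeks", for reporting engagement. The abstract says that WP3 will "determine illness trajectories and how these are affected by use of the DHI".

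Two further statements matter. Usage and engagement plans to identify baseline clinical factors that influence uptake and use. Data collection says that, after baseline, patients complete only the questionnaires that they and the clinician consider clinically relevant.

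**The concern.** Logins, completed assessments and clinician messages all accrue after registration, over the same time axis on which symptoms evolve. If symptoms drive usage, usage predicts outcome even when the app does nothing. Recovered patients may stop logging in, very fatigued patients may stop too, and clinicians may message those who worsen. These push the association in different directions, so its sign cannot be read as benefit or harm.

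Assessments completed has a further problem. Questionnaires completed on the app supply the outcome data, so the count is partly a measure of how often the outcome was observed.

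The label also claims too much. A mediation analysis splits the effect of a treatment contrast into paths. A single arm has no such contrast, so regression on usage does not estimate a mediated effect.

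At stake is the study's evidence on which components and how much engagement go with improvement. WP3 Outputs promises estimates of the programme's impact on trajectories, and Equality carries uptake into interaction terms.

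**Working it through.** **Plan's own figure.** The article gives none for this analysis. Its one precision figure (±3.2% for a proportion, 1000 patients) does not bear on the point. The check is therefore a simulation with a true app effect of exactly zero.

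**Input from the article:** n = 1000, the year 1 target.

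**Assumed inputs, not in the article:** true baseline WSAS mean 20, SD 9; individual slopes mean -0.25 and SD 0.25 points per week; residual SD 4; weekly logins Poisson with

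log rate = log(1.5) + N(0, 0.6) + g × (current true WSAS - 20)/9.

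Here g is the strength with which symptoms drive logins. At g = 0.2 the login rate rises by a factor exp(0.2) = 1.22 per 9 points; at g = 0.4, by exp(0.4) = 1.49. Negative g means that sicker patients log in less. Usage is log(1 + logins), standardised.

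**Results: WSAS points per SD of usage, with rejection rate of a 5% test**

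| Analysis | g = 0 | g = ±0.2 | g = ±0.4 |
|---|---|---|---|
| Random-slope form, usage × time, visits at weeks 0, 4, 8, 12 (per 12 weeks) | about 0; 5% | ±0.15 to 0.16; 13-14% | ±0.27 to 0.29; 29-32% |
| Same data, usage as main effect | about 0; 5% | ±2.7; 100% | ±4.8; 100% |
| Change over weeks 0-12 on logins in weeks 1-12, adjusted for baseline | about 0; 5% | ±0.64; 89-90% | ±1.34 to 1.39; 100% |
| Change over weeks 4-12 on logins in weeks 1-4, adjusted for week 0 and 4 scores | 0; 4% | ±0.25; 28-32% | ±0.51 to 0.53; 76% |
| Change over weeks 12-24 on logins in weeks 1-12, adjusted for week 0 and 12 scores | about 0; 4% | ±0.30 to 0.33; 31% | ±0.61 to 0.64; 74-78% |

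The sign follows g. If sicker patients log in less, usage looks beneficial; if they log in more, it looks harmful.

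**Tertile contrast.** A second null simulation compared high with low tertiles of 12-week logins, adjusted for baseline. Slopes had mean -3 and SD 5 points per 12 weeks, and the login rate changed by exp(-0.3) = 0.74 or exp(0.3) = 1.35 per 10 points. The false difference at week 12 was about 2.4 points in either direction. Without between-person variation in login habit it was about 7.5. A week-4 landmark adjusted for baseline and week-4 scores cut these to about 0.3-0.4 and 1.1.

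**What ordering achieves.** Against the same-window change analysis, the week-4 landmark cuts the bias from 0.64 to 0.25 and from about 1.37 to about 0.52, partly because it covers 8 weeks instead of 12. Per 12 weeks, 0.25 × 12/8 = 0.37, which is still below 0.64 but above the 0.15 to 0.16 of the random-slope form. The remainder arises because logins follow true severity while the model adjusts for scores measured with error.

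**The case against.** Several points on the other side stand.

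- **No window is stated.** A reader might infer that logins are totalled over the first 12 weeks and used to explain outcomes in those same weeks. The article does not say so. The 12-week count belongs to the reporting of engagement, and the mediation paragraph names neither window nor total. Time-varying or lagged usage would fit its words, and an analysis plan could specify it. What stands is that nothing written requires usage to precede the outcome, while the variables, the dose-response aim and the mediation label are fixed.
- **The large figures depend on the model.** The tertile contrast is not a model that the article describes. The form closest to its random-slope models and its interest in change is usage by time, where the bias is smallest. The main effect largely restates that severity and login frequency are correlated.
- **The claim is already limited.** Strengths and limitations calls the analysis exploratory, words it as association, and names the missing comparator as the major limitation. The Discussion leaves causal evidence to a separate cluster randomised trial. This lowers the severity. It does not settle the sign, and the abstract and WP3 Outputs still speak of effect and impact.
- **Ordering is not a cure.** A reader might infer that a landmark brings the bias to zero. That happened only when every weekly score to week 4 was available and logins depended on nothing else. The article schedules no weekly WSAS and expects substantial missing questionnaires.
- **New content differs.** Content is updated every few months, so its release is not driven by an individual patient's symptoms, and the same patient-level reverse causation does not apply.
- **Assessments completed is not simply the WSAS count.** It may cover several questionnaires. Hence it is only partly the outcome-observation process.

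**Conclusion.** The point holds in limited form. As described, the usage analysis cannot separate an effect of the app from an effect of symptoms on usage, and the article gives its own reasons to expect the latter. With no true effect, the association can take either sign. Its size ranges from about 0.15-0.3 WSAS points per 12 weeks (per SD of usage, random-slope usage-by-time form) to 2.7-4.8 points for a usage main effect and about 2 to 8 points for a same-window tertile contrast. All of these rest on assumed variances and an assumed symptom-to-login link; with no such link, every form rejects at about the nominal 5%. Part of the association is confounding by severity or prognosis, not strict reverse causation. The documents do not support saying that the plan commits to a same-window total, or that any one of these figures is the expected bias. This is a worthwhile, inexpensive improvement to an exploratory analysis.

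**What to change.** 1. Relate usage accrued before each outcome to subsequent change: lagged cumulative usage up to the previous assessment, or a landmark such as week 4. The time-stamped page views listed under Data collection already allow this for app usage.
2. Adjust for baseline and the questionnaire scores available up to that point, in addition to the demographic terms.
3. Treat clinician messages and dashboard reviews the same way.
4. Do not interpret assessments completed as a dose.
5. Call the analysis an association of prior engagement with subsequent change, and drop the word mediation.
6. State that residual confounding by unrecorded severity or prognosis remains, and that ordering reduces the bias without removing it.
7. Report the introduction of new content separately, since its timing is not set by the individual patient's symptoms.

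The cost is wording and programming, with no new data collection. Patients without a questionnaire by the landmark are lost or need imputation, which matters given the missing data that the article expects, and the resulting claim is more modest.

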**Trial registration number:**

Research Registry number: researchregistry6173.

Strengths and limitations of this studyStrengths include our interdisciplinary approach, which by combining methods common to engineering/computer science, for example, user-centred design and the human computer interaction lifecycle, with those from biomedicine, such as the Medical Research Council Complex Interventions Framework, promotes the likelihood of an intervention which is not only usable and acceptable, but also effective.Strong patient and public involvement input has helped define user requirements, including conceptualisation of long COVID-19 and focusing on function, fatigue and brain fog as well as ensuring the evaluation measures outcomes of interest to patients and clinicians.Intertwining service and research has enabled the rapid development and deployment of an evidence-based intervention, enabling treatment to reach patients rapidly during the pandemic.Our major limitation is the absence of a comparator group for the evaluation of effectiveness; our focus will be on profiling heterogeneity in recovery trajectories and conducting an exploratory mediation analysis to assess which intervention components and measures of app usage/engagement are associated with change in outcomes.

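### A usage term added to the random-intercept and random-slope models can pool differences between patients with changes within a patient, so it cannot support a dose-response or mediation reading unless the two are separated

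*Protocol article*

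**What the plan says.** The WP3 section on mediation analysis of intervention components says of patient usage: "number of logins and assessments completed) will be added to longitudinal models as explanatory factors". The same section sets out to look for a dose-response "relationship between usage of the app/introduction of new content and change in outcomes". Clinician activity is handled more loosely: "We will explore whether increased engagement by clinicians" is linked with better outcomes, with no statement of how it would enter a model.

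The longitudinal models are described under Recovery trajectories: "Models will include random slopes and intercepts, allowing for individualised differences in severity of baseline symptoms and subsequent trajectories". Their covariates are demographic: "Fixed effects will include age, gender, ethnicity, IMD and educational attainment". Neither motivation nor digital skill is listed. Propensity score methods are mentioned only for the synthetic comparator analysis.

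The strengths and limitations list gives the status of the analysis: "conducting an exploratory mediation analysis to assess which intervention components and measures of app usage/engagement are associated with change in outcomes". The WP3 data collection section confirms that use is time-stamped: "Usage data including the date and time of each page view by each patient are recorded automatically by the programme".

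**The concern.** A usage coefficient in a model with patient random effects is free of bias only if usage is independent of those random effects. That is doubtful here. The article itself expects patients with low digital literacy to need support to engage, and plans to identify baseline clinical factors that influence use. People who log in more may also be people who recover at a different rate.

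Only the within-patient comparison bears on dose-response, and the article does not separate it from the between-patient one. With no comparator group, this analysis is one of two stated focuses of the evaluation, so a false usage effect would carry weight.

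**Working it through.** **The plan's own figure.** The article gives none for this analysis. Its only sample-size figure, ±3.2% for 1000 patients, reproduces as 2 × √(0.25/1000) = 3.16%. It concerns an engagement proportion and plays no part here.

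**Step 1: where the bias comes from.** Let u be a stable unmeasured trait and let the app have no effect.
- Outcome: y = a + (b + d·u)·t + patient effects + error, where d links the trait to recovery rate.
- Usage in an interval: L = c + k·u + g·u·t + noise. Here k links the trait to use, and g lets use change over time differently by trait.
- Patient mean: c + (k + g·t̄)·u + mean noise.
- Deviation from that mean: g·u·(t − t̄) + noise.

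A single term L carries u, so it picks up part of d·u·t. If g = 0, the deviation is free of u. If g ≠ 0, the deviation contains a trait-by-time part that lines up with d·u·t. A mean-by-time term then supplies a proxy for u·t.

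**Step 2: inert app, 1000 patients, 4 visits.** All inputs are assumptions, because the article gives none: trait–usage correlation 0.4; trait–level or trait–slope correlation 0.3; usage ICC 0.5; level SD 8; slope SD 1.2 per 4 weeks; residual SD 5; 20% of the trait captured by a covariate. The weak row uses 0.2 and 0.15. There were 60 data sets per row, so the Monte Carlo SE is at most √(0.25/60) = 6.5 points. Entries are false-positive rates at nominal 5%.

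| Trait linked to | Interval logins, single term | Interval, deviation | Cumulative, single term | Cumulative, deviation | 12-week total × time |
|---|---|---|---|---|---|
| Neither | 0% | 0% | 3% | 5% | 3% |
| Level, weak | 2% | 0% | 5% | 3% | 2% |
| Level | 15% | 0% | 13% | 5% | 3% |
| Slope | 0% | 2% | 40% | 40% | 40% |
| Level and slope | 18% | 0% | 75% | 40% | 40% |
| Level and slope, 80% of trait measured | 2% | 0% | 43% | 43% | 37% |

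In the level row the mean coefficients for interval logins are −0.132 (single), −0.857 (between) and −0.023 (within). The weight on the between-patient part is (0.132 − 0.023)/(0.857 − 0.023) = 0.109/0.834 = 0.13, so the single term is a blend.

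**Step 3: interval use when the trait acts on slope only.** Assumed: 600 patients, six possible scores each 50% observed, baseline-adjusted, 60 data sets.

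| Trait–usage, trait–slope correlation | Single term | Cumulative | Deviation |
|---|---|---|---|
| 0.4, 0.3 | 13% | 40% | 7% |
| 0.6, 0.5 | 43% | 98% | 5% |

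The same layout was run with trait effects set directly: 0.5 or 0.3 on log-logins, and −0.6, −0.2 or 0 points per 4 weeks on slope. The single term was significant in 40% of 40 data sets (stronger trait), 3% of 30 (weaker) and 0% of 30 (no slope link).

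**Step 4: does splitting suffice?** Not when use declines faster in some patients than in others. With an assumed trait-by-time effect on log-logins of 0.12 or 0.20, the deviation term was falsely significant in 20% and 30% of 30 data sets. In a further set with a stronger trait link it was significant in 70% and 98%, against 100% for the single term. Adding patient mean × time brought the deviation term to about 5% in those scenarios.

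**Step 5: limit of that repair.** By the algebra in step 1, mean × time removes slope confounding only as far as the patient's mean use measures the trait. If mean use also varies for unrelated stable reasons, some bias in the deviation term remains.

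**The case against.** **Model form is not fixed.** The article does not say whether logins are per interval, cumulative or a total. Its only usage definition, under Usage and engagement, is a 12-week total, which has no within-patient part. Centring of covariates is detail that an article may leave to a fuller document. This stands as a reason for caution: the blend arises only if a time-varying term is used. It does not rescue the total, which is a purely between-patient comparison and gave 40% false positives for change when the trait acted on slope.

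**Exploratory wording.** The analysis is called exploratory and associational, the missing comparator is named as the major limitation, and the Discussion looks to a cluster randomised trial for causal evidence. That is fair context. It does not protect the terms mediation and dose-response, which the analysis section uses for the same coefficients.

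**Demographic adjustment.** Age, education and IMD may stand in for part of digital skill. This stands in part. With 80% of the trait measured, interval logins fell to 2%, but total × time stayed at 37% and reached 7% only when the covariate was also allowed to act on slope.

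**Clinician activity.** A reader might infer that clinician messages and reviews are also entered directly in these models. The article says only that their link with outcomes will be explored, so the point applies to them only if they are entered as time-varying terms.

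**Conclusion.** The point holds as a possibility that the described analysis does not guard against. A single time-varying usage term pools between-patient and within-patient information, and an unmeasured stable trait linked to use and recovery rate can then produce a usage effect for an inert app.

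A reader might go further and conclude that the planned analysis will credit an inert app. The documents do not support that: they give no strength for any such link. Error was about nominal with weak links and reached 75% to 100% in the worst cases simulated. All these rates rest on assumed inputs and small numbers of data sets, so they show direction and range and do not predict this study's error rate.

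Nor should a reader infer that splitting usage is a full cure. It did not correct cumulative logins when the trait acted on slope, cannot be applied to a 12-week total, and needs the mean-by-time term when usage trends differ between patients. A change is still worth making, because a better model is available from data already recorded.

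**What to change.** For patient usage measured per interval, enter three terms: the patient's own mean, that mean by time, and the deviation of the preceding 4-week interval from that mean. Base any dose-response statement on the deviation term. Report the mean terms, and any 12-week or cumulative total, as descriptive associations. Treat clinician messages and reviews the same way if they are entered as time-varying terms.

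State in the plan that the deviation term remains open to time-varying confounding, for example patients logging in because symptoms have changed, and that mean × time adjusts for a stable trait only as well as mean use reflects it.

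The cost in data is nil, since page views are already dated; the work is a few derived variables per exposure. The statistical cost is a wider interval for the within-patient term and reliance on patients with at least two post-baseline scores. Those patients may be selected: after baseline, PROMs are completed only where judged clinically relevant, and the Discussion expects substantial missing data. Report how many patients contribute to the deviation term and how they differ from the rest.
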